#### Video-based follow-up meetings with study participants

Within one to 2 weeks after the initial medication interview, the clinical pharmacist schedules a video-based follow-up meeting with the participant. The purpose of this first follow-up meeting is to check whether the participant has understood and initiated the recommended changes in their medication therapy. The purpose is also to answer questions and to assess if any new problems have emerged regarding the participant’s medication therapy. For some participants, the structured medication review may result in multiple medication-related changes, while other participants will not need any changes in their medication regimen. Two additional follow-up meetings are scheduled and will take place four and twelve weeks after the initial medication interview. The purpose of these meetings is to check on the participant’s progress and experiences of their medication therapy. The clinical pharmacist also asks questions regarding practical aspects of the participant’s medication management, medication adherence and the occurrence of possible side effects. Due to practical reasons, all three follow-up meetings can be re-scheduled to the nearest available date.

#### Additional meetings with the participant or the primary care physician

Additional meetings can be scheduled if requested by the participant or the PCP, or if considered necessary by the clinical pharmacist. For example, the clinical pharmacist may seek additional contacts with the participant or the PCP due to medication-related questions or discovery of additional MRPs.

#### Electronic medical record reviews

The clinical pharmacist conducts electronic medical record reviews once every 2 weeks during the 12-week study period. This activity is conducted to discover abnormal laboratory values, unanswered referrals, to detect whether the participant has had any new changes in their medication regimen, or relevant contacts with healthcare services. Additional MRPs may be discovered, and the electronic medical record reviews also serve as an important basis for the video-based follow-up meetings with the participant.

### Data collection and outcomes

Data will be collected through participants’ electronic medical records, during video-based meetings with participants and PCPs, and through self-report questionnaires.

Participant data needed to perform a structured medication review, such as age, sex, current diseases and medical history, will be extracted from the participants’ electronic medical records (table 2). Additional participant data, such as the use of OTC medications and supplements, medication management issues, as well as symptoms and potential side effects, will be collected orally and documented on data collection forms during the video-based meetings with the participants. PCPs’ acceptance rate of pharmacists’ recommendations will be assessed during the video-based interdisciplinary meetings with the PCPs. Complete data collection forms will be made available on reasonable request.

**Table 2 T2:** Variables and outcome measures

Variables	Description	Source of data	Time interval/timing
Participant characteristics	Age, sex, height, weight, laboratory values, current and previous diseases, current and previous medications or treatments, medication management issues, symptoms and side effects	EMR, VBM-P	12-week study period
MRPs and clinical pharmacists’ recommendations	Identification and classification of MRPs, clinical pharmacists’ recommendations to resolve MRPs, physicians’ acceptance rate of pharmacists’ recommendations	SMR VBIM-PCP VBM-P	12-week study period
Medication adherence	MARS-5	SRQ	Baseline and after 12 weeks
Health-related quality of life	EQ-5D-5L	SRQ	Baseline and after 12 weeks
Beliefs about medicines	BMQ	SRQ	Baseline and after 12 weeks

BMQ, Beliefs about Medicines Questionnaire; EMR, Electronic medical records; EQ-5D-5L, EuroQol-5D-5L questionnaire; MARS-5, Medication Adherence Report Scale; MRPs, Medication-related problems; SMR, Structured medication review; SRQ, Self-report questionnaire; VBIM-PCP, Video-based interdisciplinary meeting with primary care physician; VBM-P, Video-based meeting with participant.

Self-report questionnaires will be used to measure participants’ self-reported medication adherence (MARS-5), health-related quality of life (EuroQol-5D-5L (EQ-5D-5L)) and beliefs about medicines (BMQ) (table 2). The data will be collected when the participants enter the study (baseline) and at the end of the 12 week study period. In accordance with the baseline questionnaires, the follow-up questionnaires will be sent to the participants by mail, after the last follow-up meeting that occurs around 12 weeks after the initial video-based meeting. Incomplete questionnaire responses will be excluded from the analyses.

In addition, for future process evaluation purposes, the clinical pharmacists will document the time required for each activity per participant.

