### Sample size

The aim is to include 100 participants. This sample size serves the dual purpose of describing the prevalence of MRPs within the study population with good precision and enabling the statistical evaluation of changes in key outcome measures (eg, self-reported medication adherence, measured dichotomously) from baseline to the end of the study through intra-individual comparisons. No comparison group is included.

A priori power calculation has been performed to size the study with respect to the intra-individual comparison of the proportion of adherent participants. Based on the assumptions of a clinically relevant increase in the proportion of adherent participants from 85% at baseline to 95% at the end of the study (ie, an absolute difference of 10 percentage points), and an expected correlation (phi coefficient) of 0.6 between the two measurement time points, 80 participants are required to achieve 80% statistical power to detect this difference using a two-sided McNemar’s test at a 5% significance level (α=0.05), with continuity correction applied. The assumptions about the proportions of adherent participants are based on results from previous studies on self-reported medication adherence using the Medication Adherence Report Scale (MARS-5) questionnaire.^36 37^

Since the planned inclusion is 100 participants, which exceeds the calculated requirement of 80, the study will have >80% power to identify a difference of this magnitude under the given assumptions. The sample size also accounts for a potential dropout rate of 20%. The sample size of 100 participants is therefore considered well-justified and adequate to meet the study’s descriptive aims and allow for meaningful analyses of changes over time.

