#### Medication adherence

Participants’ self-reported medication adherence will be assessed through the Swedish version of the MARS-5.^33 42^ This validated questionnaire consists of five questions describing non-adherent behaviour that is scored on a five-item Likert scale: 1=always, 2=often, 3=sometimes, 4=rarely and 5=never. The sum score ranges between five and 25 points, where a higher score indicates higher levels of self-reported medication adherence. MARS-5 scores will be dichotomised into adherent/non-adherent. The cut-off score will be >22, in accordance with previous studies.^36 43^

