#### Beliefs about medicines

Participants’ beliefs about medicines will be assessed through the Swedish version of the Beliefs about Medicines Questionnaire (BMQ).^35^ This validated questionnaire consists of two sections, BMQ-General and BMQ-Specific. BMQ-General assesses the respondents’ beliefs about medicines in general and BMQ-Specific evaluates beliefs about medicines prescribed for the respondents’ personal use. BMQ-General consists of three subscales (*harm, overuse* and *benefit*), while BMQ-Specific consists of two subscales (*necessity* and *concern*). The questionnaire consists of 22 questions that are scored on a five-item Likert scale: 1=strongly disagree, 2=disagree, 3=uncertain, 4=agree and 5=strongly agree.

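### Excluding every incomplete questionnaire, read as whole-form deletion, throws away usable secondary-outcome data, and the sample size has no allowance for the loss

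*Protocol article*

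**What the plan says.** The rule is one sentence under Data collection and outcomes: "Incomplete questionnaire responses will be excluded from the analyses". No exception is given for an item, a subscale or a scale. Data analysis and statistics adds only that suitable methods will be used for the baseline-to-end comparisons.

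The rule applies to three mailed instruments, each completed at baseline and after 12 weeks:

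- **MARS-5** (Medication adherence): five items scored 1 to 5, summed to a total of 5 to 25 and dichotomised. "The cut-off score will be >22, in accordance with previous studies".
- **BMQ** (Beliefs about medicines): "The questionnaire consists of 22 questions that are scored on a five-item Likert scale". The items form five subscales, and Data analysis and statistics states an expected direction of change for each.
- **EQ-5D-5L** (Health-related quality of life): five dimensions plus a separate VAS.

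The Sample size section is built on the MARS-5 comparison. It assumes a change "from 85% at baseline to 95% at the end of the study", with "an expected correlation (phi coefficient) of 0.6 between the two measurement time points", tested by a "two-sided McNemar’s test at a 5% significance level (α=0.05), with continuity correction applied". It concludes that "80 participants are required to achieve 80% statistical power to detect this difference". It also says "The aim is to include 100 participants", and describes this number as covering 20% dropout.

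**The concern.** Read plainly, the rule makes the returned form the unit: any blank disqualifies it. That is stricter than the analyses need. The BMQ subscales are interpreted separately, so a blank in the harm subscale is no reason to lose a completed necessity or concern score. The EQ VAS does not depend on the five dimension questions. A MARS-5 form with four of five answers still carries most of the information about adherence, and sometimes settles the classification.

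These are before-after comparisons, so a blank at either occasion costs the pair. The dropout allowance is used up by people who leave or do not return a form. Any pair lost to an incomplete form therefore takes the adherence comparison below its stated requirement. The BMQ is most exposed, because a pair needs 44 answers. At stake are the precision of three named secondary objectives and the power of the one comparison that was sized.

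**Working it through.** **1. The plan's own figure.** Inputs from Sample size: p1 = 0.85, p2 = 0.95, d = 0.10, φ = 0.6, two-sided α = 0.05, power 80%.

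- Both-adherent cell: p11 = p1·p2 + φ·√(p1q1p2q2) = 0.8542.
- Discordant proportion: ψ = p1 + p2 − 2·p11 = 0.0916.
- n0 = [1.96·√ψ + 0.842·√(ψ − d²)]² / d² = 69.5.
- With continuity correction: n = (n0/4)·[1 + √(1 + 2/(n0·d))]² = 79.2, so 80. The stated figure is reproduced.
- Dropout: 100 × 0.80 = 80. The margin for anything else is zero.

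**2. Which φ to use for power.** With φ = 0.6 the adherent-to-non-adherent cell is 0.85 − 0.8542 = −0.0042, which is impossible. The largest φ these margins allow is 0.546 (that cell = 0, ψ = 0.10). This is a separate matter from the exclusion rule. I use 0.546 because it is the most favourable feasible value at these sample sizes, so the powers below are upper limits.

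**3. Pairs left under whole-form deletion.** The article gives no item non-response rate. Assume each item is blank independently at rate r. A complete MARS-5 pair needs 10 answers and a complete BMQ pair needs 44:

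| r (assumed) | MARS-5: (1−r)^10 | of 80 | BMQ: (1−r)^44 | of 80 |
|---|---|---|---|---|
| 0.5% | 0.951 | 76 | 0.802 | 64 |
| 1% | 0.904 | 72 | 0.643 | 51 |
| 2% | 0.817 | 65 | 0.411 | 33 |

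**4. Power of the MARS-5 comparison.** At φ = 0.546 all discordant pairs go one way. The corrected statistic (m − 1)²/m exceeds 3.84 first at m = 6 (25/6 = 4.17; at m = 5 it is 16/5 = 3.2). Exact power is therefore P[Bin(n, 0.10) ≥ 6]. The φ = 0.5 column is a full enumeration, and the last column is the plan's own formula with φ = 0.6:

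| Pairs | Exact, φ = 0.546 | Exact, φ = 0.5 | Plan's formula, φ = 0.6 |
|---|---|---|---|
| 80 | 82% | 77% | 80.5% |
| 76 | 78% | 74% | 78% |
| 72 | 74% | 69% | 75% |
| 65 | 64% | 61% | 70% |

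**5. What a partly answered MARS-5 shows.** With one blank and answered sum S, the total lies between S + 1 and S + 5. If S ≤ 17 the total cannot exceed 22, so the person is certainly non-adherent. If S = 20 the total could still be 21, so adherence is never certain.

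**6. Does deletion bias adherence?** It depends on who skips items. At one time point, with blank rates rA among adherers and rN among non-adherers, the complete-case proportion is p(1−rA)^5 / [p(1−rA)^5 + (1−p)(1−rN)^5].

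- rA = rN: 0.85 stays 0.85 and 0.95 stays 0.95.
- rN = 5%, rA = 1%: 0.85 becomes 0.874 and 0.95 becomes 0.959. The levels rise, but the change falls from 10.0 to about 8.5 points.
- rA = 5%, rN = 1%: 0.85 becomes 0.822 and 0.95 becomes 0.939. The levels fall, and the change rises to about 11.7 points.

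**7. Would rescuing only the provable non-adherers help?** In a simulation with true adherence 0.861 and 5% random blanks, complete cases gave 0.861. About 77.3% of forms were complete, and 10.4% of the incomplete ones were provably non-adherent. Adding back only those gives (0.861 × 0.773) / (0.773 + 0.104 × 0.227) ≈ 0.835, which is a downward bias.

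**The case against.** **The unit is not stated.** The sentence is compatible with exclusion scale by scale, and scoring detail is often left to an analysis plan. This stands in part. With about 4 to 5 items per BMQ subscale (22 over five), a subscale pair needs 8 to 10 answers, so about 90–92% of pairs survive at 1% blanks and 82–85% at 2%. The heavy BMQ loss belongs to the whole-form reading only. But the article does state a rule, and as worded it permits that reading.

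**The loss is conditional.** The blank rates are assumptions, and the shortfall needs the full 20% dropout. This stands. With no dropout, 100 enrolled leave about 95, 90 or 82 MARS-5 pairs, all above 80. But 20% is the dropout the plan itself provides for. BMQ losses do not touch the stated power, which concerns MARS-5 alone.

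**Bias.** A reader might infer that the rule inflates adherence, because an incomplete form can prove non-adherence and never adherence. The documents do not support that. The asymmetry lies in what a partial form can prove. Deletion also removes adherent people who left a blank, and nothing in the article links skipping items to adherence. Step 6 shows no bias under random blanks and either direction otherwise.

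**Stakes.** MRPs are the primary outcome, are reported descriptively and are untouched. The Discussion already acknowledges response bias in the questionnaires. Both points are correct, and they limit the importance of the matter.

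**Conclusion.** The point holds in a limited form. As worded, the rule allows usable data to be discarded on three secondary outcomes, and the sample size leaves no room for that loss.

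For MARS-5, at assumed blank rates of 0.5%, 1% and 2% and with the planned 20% dropout, about 76, 72 and 65 pairs remain, with exact power of at most about 78%, 74% and 64%. For the BMQ, with the whole form as the unit, about 64, 51 and 33 pairs remain. These figures rest on independent blanks at rates the article does not give.

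Bias in adherence is possible but not established, and its direction cannot be determined from the article. It should not be described as upward. Nor should a large BMQ loss be stated without both conditions: the blank rate and the whole-form reading. This is worth changing before analysis, but it does not threaten the primary objective.

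**What to change.** Replace the exclusion sentence with a rule for each analysed quantity:

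- **Unit.** Judge completeness separately for the MARS-5 total, each EQ-5D-5L dimension, the VAS and each BMQ subscale. A blank in one does not remove another.
- **BMQ.** Prorate a subscale when at least half of its items are answered; otherwise treat that subscale alone as missing.
- **MARS-5.** Use item-level multiple imputation that keeps the answered items fixed, then sum and dichotomise. Provable non-adherers are then always classified correctly, and undetermined forms contribute in both directions. Report complete cases as a sensitivity analysis. Do not classify only the provable non-adherers while dropping the undetermined forms, because that pulls adherence down (step 7).
- **Prevention.** Baseline forms come back before the pharmacist's phone call (Recruitment of study participants), so skipped items can be asked for then. Follow-up forms are mailed after the last meeting, when no further service contact is scheduled, so the analysis rule matters most there.

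The cost is a few lines of text, slightly more programming and a short addition to a call already planned. The downside is that imputation relies on blanks being missing at random given the answered items; the complete-case analysis shows how far the result depends on the handling of blanks.

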#### Medication-related problems (MRPs)

MRPs are the primary outcome of this study. The MRPs will be classified according to a modified version of the well-known classification system by Cipolle *et al:*^40^
*unnecessary drug therapy, needs additional drug therapy, ineffective/inappropriate drug, dosage too low, dosage too high, adverse drug reaction, non-adherence, drug interactions, monitoring need* and *other*. MRPs will be identified during the entire study period, for example through the structured medication review, by reviewing the participants’ electronic medical records and during the video-based meetings. The clinical pharmacists’ recommendations to resolve MRPs will be classified according to a modified version of the system developed by the French Society of Clinical Pharmacy:^41^
*discontinuation of medication therapy, initiation of medication therapy, dose adjustment, switch medication, optimisation of administration, medication monitoring, information to/discussion with the patient* and *other*. Physicians’ acceptance rate of pharmacists’ recommendations will be classified as *accepted recommendation, rejected recommendation* or *unknown*.

#### Medication adherence

Participants’ self-reported medication adherence will be assessed through the Swedish version of the MARS-5.^33 42^ This validated questionnaire consists of five questions describing non-adherent behaviour that is scored on a five-item Likert scale: 1=always, 2=often, 3=sometimes, 4=rarely and 5=never. The sum score ranges between five and 25 points, where a higher score indicates higher levels of self-reported medication adherence. MARS-5 scores will be dichotomised into adherent/non-adherent. The cut-off score will be >22, in accordance with previous studies.^36 43^

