### Study population and recruitment

#### Eligibility criteria

People will be eligible for inclusion if they are (1) ≥65 years, (2) Living at home (ie, not in a nursing home), (3) Registered at primary healthcare centres in rural municipalities within Västerbotten County (and neighbouring counties if necessary) and (4) Using five or more prescribed medications and/or considered as a potential candidate by the primary care physician (PCP). An example of a potential candidate would be a person with multimorbidity, where a structured medication review could potentially improve patient’s medication-related outcomes. According to national regulations, people ≥75 years with at least five prescribed medications are entitled to receive a medication review once a year in primary care.^31^ In the present study, people aged 65 years or older will be included, as people ≥65 years are defined as older people, according to the statistical office of the European Union (Eurostat).^32^ People will be excluded if they are (1) Unable to communicate, (2) Do not speak Swedish, (3) Have a confirmed major neurocognitive disorder or (4) Receive palliative care.

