### Data analysis and statistics

Descriptive statistics, for example, frequencies and proportions, will be used to present MRPs. Due to the single-arm design, no comparative analyses will be performed.

Self-reported medication adherence, beliefs about medicines and health-related quality of life will be compared between baseline and the end of the study using appropriate statistical methods. Regarding self-reported medication adherence, an increase of approximately 10 percentage points is expected. Regarding beliefs about medicines, a moderate increase is expected for positive beliefs (benefit and necessity), while a moderate decrease is expected for negative beliefs (harm, overuse and concern). Regarding health-related quality of life, a moderate positive change is expected. Statistical analyses will also be performed to investigate associations between beliefs about medicines and self-reported medication adherence and various demographic factors such as age, sex and number of medications.

Regarding the semi-structured interviews, the interviews will be audio-recorded, transcribed verbatim and analysed using reflexive thematic analysis.^46 47^

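### Adherence change is judged only at MARS-5 >22, so on the plan's own 85% baseline about 15 of 100 participants can register improvement; a paired comparison of the sum score should accompany it

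*Protocol article*

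**What the plan says.** The Medication adherence section of the protocol article defines a MARS-5 sum score from 5 to 25, higher being better, and then fixes its use: "MARS-5 scores will be dichotomised into adherent/non-adherent. The cut-off score will be >22, in accordance with previous studies". A score of 23, 24 or 25 therefore counts as adherent.

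The Sample size section plans for "a clinically relevant increase in the proportion of adherent participants from 85% at baseline to 95% at the end of the study", with "an expected correlation (phi coefficient) of 0.6 between the two measurement time points", and tests it "using a two-sided McNemar’s test at a 5% significance level (α=0.05), with continuity correction applied". The result is that "80 participants are required to achieve 80% statistical power to detect this difference"; 100 are to be enrolled to allow for 20% dropout.

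The Abstract names two-sided McNemar's tests for the questionnaire outcomes. The Data analysis and statistics section leaves the methods general but repeats the target: "Regarding self-reported medication adherence, an increase of approximately 10 percentage points is expected".

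Eligibility depends on age, living at home, registration at a rural centre, and number of medicines and/or physician nomination. There is no adherence criterion. Adherence is a secondary objective, but it is the only outcome with a power calculation.

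**The concern.** On a yes/no endpoint, anyone already in the yes category can only stay or fall. With 85% assumed adherent at the start, any improvement has to come from the remaining 15%.

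The cut-off also decides which changes are seen. A participant who rises from 12 to 22 counts as unchanged, while one who rises from 22 to 23 counts as a success. A fall from 25 to 23 and a rise from 23 to 25 both go unrecorded. The full score is collected at both time points, but the article gives it no part in the before–after comparison.

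What is at stake is interpretation. A non-significant McNemar result could mean that adherence did not change, or that it changed where the dichotomy cannot register it. As described, the comparison cannot tell these apart.

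**Working it through.** **Inputs** (Sample size and Medication adherence sections): p1 = 0.85, p2 = 0.95, difference d = 0.10, phi = 0.6, two-sided α = 0.05, power 80%, 80 completers, 100 enrolled, cut-off >22.

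**1. The plan's own figure.** The paired cells follow from the margins and phi:

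- √(0.85 × 0.15 × 0.95 × 0.05) = 0.0778
- Adherent at both times: 0.85 × 0.95 + 0.6 × 0.0778 = 0.8542
- Adherent to non-adherent: 0.85 − 0.8542 = −0.0042
- Non-adherent to adherent: 0.95 − 0.8542 = 0.0958
- Discordant total pd = 0.0916

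n = (1.96√pd + 0.8416√(pd − d²))²/d² = 69.5. The continuity correction raises this to 79.2 by n/4 × (1 + √(1 + 2/(nd)))², or 79.5 by n + 1/d. Both round up to 80, and 80/0.80 = 100. The stated figure is reproduced, so the calculation does use the 85% baseline. (The negative cell shows that phi = 0.6 is not attainable with these margins; the maximum is 0.0425/0.0778 = 0.546. That is a separate matter, relevant here only in step 4.)

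**2. Who can register improvement.** 100 × (1 − 0.85) = 15; 80 × 0.15 = 12. If 85% is the true proportion, the 95% binomial ranges are 8–22 of 100 and 6–19 of 80.

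**3. Share of them who must convert.** The net gain is 10 per 100. If nobody slips, 10/15 = 67% (8 of 12 among completers).

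**4. Effect of slippage.** If s per 100 go from adherent to non-adherent, the share needed is (10 + s)/15, and the implied phi is ((0.85 − s/100) − 0.8075)/0.0778.

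| s per 100 | Share of non-adherent who must convert | Implied phi |
|---|---|---|
| 0 | 67% | 0.546 |
| 0.4 | 69% | 0.5 |
| 1.9 | 79% | 0.3 |
| 3 | 87% | 0.16 |

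Only the first row follows from the plan's margins without a further assumption. The others are illustrations. The 3-per-100 row in particular implies a correlation far below the stated 0.6.

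**5. What the planned test needs.** Let b be the number who improve and c the number who slip. The corrected test is significant when (|b − c| − 1)²/(b + c) > 3.84. Take the expected 12 non-adherent among 80 completers:

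- c = 0: b = 6 suffices (25/6 = 4.17)
- c = 1: b = 8 (36/9 = 4.00)
- c = 2: b = 10 (49/12 = 4.08)
- c = 3: all 12 (64/15 = 4.27)
- c = 4: not significant even if all 12 improve (49/16 = 3.06)

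This describes the test at one expected baseline count and does not predict how many will slip. It also shows that with no slippage significance needs 6 of 12, fewer than the 8 of 12 in the anticipated effect.

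**6. What the score could add.** MARS-5 has five items scored 1 to 5, so one item moving from never to rarely takes a total of 23 to 22 and changes category. The same one-point step from 25 to 24 leaves no trace on the dichotomy but is visible on the sum score.

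**The case against.** Several objections are sound, and they limit the point.

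- **The ceiling is already in the sizing.** A reader might infer that the power calculation overlooked it. It did not: 85% is an input, as step 1 shows.
- **Not selecting for non-adherence is appropriate.** A reader might infer that the study should have recruited poor adherers. The primary outcome is medication-related problems, and the study aims to describe their prevalence in home-living older adults. Enrichment would distort that. Non-adherence is also one of the problem categories in the primary outcome, so the dichotomy is not the only information on adherence.
- **The steep conversion figures are not the plan's.** A reader might infer that 87%, or even 100%, of non-adherers must convert. The first needs 3 per 100 to slip. The second needs 5 per 100, which implies phi of about (0.80 − 0.8075)/0.0778 = −0.10. Neither agrees with the correlation the plan assumes, and the documents do not show that 67% is out of reach.
- **The sum score has a ceiling too.** The documents give no MARS-5 distribution. If most adherent participants already score 25, the score adds little room for improvement, though it would still show falls and change below the cut-off.
- **Companion analyses often sit in the analysis plan.** This is a condensed article, and a separate plan may hold one. That would answer the point. But for adherence the article does not leave the method open: it fixes the cut-off, the test and the sizing.

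What remains is that the method as stated discards information already collected, and this limits what a null result can support.

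**Conclusion.** The point holds as a cheap improvement to a secondary analysis. It is not an error in the sample size or the eligibility criteria. On the plan's own assumption about 15 of 100 participants (12 of 80 completers) can register improvement, and at least 67% of them must cross the cut-off for the expected 10-point gain. Any slippage raises that share, by an amount the documents do not fix.

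This rests on the 85% planning figure, which the observed baseline may not match, and on the dichotomy with McNemar's test being the only adherence comparison the article describes. The documents do not support the stronger inference that the adherence objective cannot be met, or that a null result would be due to the ceiling. They support only that such a result would be ambiguous without the score.

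**What to change.** Keep the >22 dichotomy with McNemar's test as the sized comparison, and add:

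1. A prespecified paired comparison of the MARS-5 sum score, baseline versus 12 weeks in the same participants, by a rank-based or similar method, as a companion secondary analysis.
2. The numbers scoring ≤22 and exactly 25 at baseline, so that readers can see how many could improve on each measure.
3. A statement that a non-significant McNemar result will not be interpreted as no change without the sum-score result.

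If a separate analysis plan already contains these, a sentence in the protocol saying so is enough. The data are already being collected, so enrolment, questionnaires and sample size do not change. The cost is one more secondary comparison, on a skewed score with its own maximum at 25, so how much it adds will depend on the baseline distribution.
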